## Abstract

**Background:**

Periprosthetic joint infection (PJI) is one of the most severe complications in hip arthroplasty, and treatment of PJI is associated with high re-infection rates and significant loss of quality of life for patients, as well as socio-economic impact to health systems. Antimicrobial coating of implants with silver is a promising option to improve the outcome of PJI. However, there is no data from randomized control trials on silver-coated versus standard non-silver-coated implants in patients with PJI. Therefore, the aim of the current study is to assess clinical outcome for the use of silver-coated hip implants (further referred to as IP-coated) versus non-IP-coated implants in patients requiring surgical revision for hip PJI.

**Methods:**

This is a multicenter confirmatory interventional randomized controlled superiority single-blinded study with two stages: pilot stage (part A) and pivotal stage (part B). Patients indicated for unilateral cementless acetabular and hip stem revision due to chronic periprosthetic infection planned for single-stage or two-stage surgical procedures are included. Patients will randomly be assigned either to the IP-coated or the non-IP-coated implant group. The primary outcome parameter is infection-free survival within 12 months after hip PJI. The underlying hypothesis is that the IP coating significantly reduces the risk of periprosthetic reinfection compared to the non-IP-coated implants. Secondary outcome parameters include data on the safety and performance of the prostheses through a 2-year clinical follow-up, including patient-related outcome parameters, such as Harris Hip Score, EQ-5D, radiographical assessment, and blood silver concentrations. An adaptive study design is planned with the inclusion of 268 subjects according to initial sample size calculations. Upon follow-up of 134 patients for 12 months or inclusion of 90% of the study patients, preliminary study results will be used to re-estimate the sample size, which may be extended up to 400 subjects.

**Discussion:**

The current study aims to fill the evidence gap for the idea of IP-coated implants to reduce re-infection rates in the treatment of hip PJI. To the authors’ best knowledge, this is the first randomized controlled superiority trial evaluating the outcome of a silver-coated versus a non-silver-coated prosthesis for the treatment of hip PJI. The adaptive study design allows an adjustment of the initial sample size to reduce the risk of an underpowered superiority.

**Trial registration:**

ClinicalTrials.gov NCT06737809 (date of publication 17.12.2024).

## Introduction

### Background and rationale {6a}

Total hip arthroplasty (THA) is one of the most frequently performed procedures in orthopedic surgery, offering significant pain relief, functional restoration, and improved quality of life for patients. Annually, over 3.1 million primary THAs are performed across Europe, with 177,826 procedures recorded in Germany alone in 2023 [1]. However, periprosthetic joint infection (PJI) remains one of the most severe complications following THA, placing a heavy burden on both patients and healthcare systems [2–5]. From prospective or registry studies, periprosthetic infection rates (or if not explicitly stated, infection-related re-revision rates) of 3.7%, 12%, 12.5%, 15.9%, 18.2%, 18.6%, 22.0%, and 23.3% have been reported after infection-related hip revision arthroplasty. Registry analyses suggest that 1-year revision rates following multiple revision surgeries may be significantly higher-by at least 49%-compared to rates after first-time revision procedures.

To address this clinical challenge, an infection prevention (IP) silver coating (further referred to as IP coating, Aesculap, Tuttlingen, Germany) will be used for hip revision prosthesis implants (Plasmafit^®^ Revision cup, Structan^®^ Augments, and Prevision^®^ Revision stem system, Aesculap, Tuttlingen, Germany) as infection prevention and for the surgical treatment of hip PJI. This novel coating developed by Bio-Gate AG, Nürnberg, Germany, is based on metallic silver embedded in a polysiloxane matrix, designed to release antimicrobial silver ions upon water contact [6, 7]. This IP coating relies on the multimodal effects of released silver ions, such as alterations to the bacterial cell respiratory system and DNA, with a broad coverage of all types of microorganisms, including gram-positive and gram-negative bacteria [8].

Preclinical and clinical data suggest that this approach can inhibit bacterial colonization at the implant surface without significantly affecting the surrounding tissue, offering a targeted strategy for the use of coating in PJI [9].

The used investigational IP-coated devices are similar to their non-IP-coated CE-certified predecessors in terms of mechanical properties and clinical indications. Clinical safety of the used silver ions in the coating has been shown recently [10]. Given the substantial burden of PJIs and the unmet clinical need for effective prevention strategies, evaluating the efficacy of IP-coated implants is both timely and clinically relevant. The proposed clinical investigation will assess whether this novel silver coating technology can significantly reduce PJI rates in PJI revision hip arthroplasty, ultimately improving patient outcomes.

### Objectives {7}

The aim of this clinical investigation is to evaluate the safety and performance of the IP-coated hip implants. The primary endpoint will assess the effectiveness of the IP-coated hip implants in reducing the risk of periprosthetic joint infection. Secondary endpoints will examine the key functional and clinical benefits of the implants, including hip joint functional restoration, radiological outcome, and pain reduction, alongside an evaluation of device safety. Non-IP-coated hip implants will be utilized as the comparator device in this study.

### Trial design {8}

This clinical investigation is a parallel-group, randomized, controlled trial with a 1:1 allocation ratio following a superiority framework. This clinical investigation consists of two stages: pilot stage (part A) and pivotal stage (part B).

The two stages of the clinical investigation allow an early assessment of short-term safety of the investigational products at the beginning (part A) with a low number of subjects. This is followed by the main clinical investigation (part B). In addition, an adaptive study design allows the extension of the sample size at interim analysis during part B.

## Methods: participants, interventions, and outcomes

### Study setting {9}

This study is carried out at 10 study sites in Poland, Spain, and Germany.

### Eligibility criteria {10}

#### Inclusion criteria

Participants eligible for inclusion in the study are male and female patients aged 18 years or older who have provided written informed consent prior to participation. Eligible participants must have been diagnosed with a periprosthetic joint infection (PJI) according to the European Bone and Joint Infection Society (EBJIS) criteria [11], with the infection classified as chronic based on the recommendations of the Pro-Implant Foundation (PIF, Berlin, Germany) [12]. These patients must be indicated for unilateral, cementless acetabular and hip stem revision surgery due to chronic periprosthetic infection, which may involve either a single-stage or two-stage surgical procedure, as determined by the clinical standards of the investigation site. Additionally, participants must be assessed by the clinical investigator as therapy compliant and capable of attending all follow-up visits required by the study protocol. Finally, only patients with an American Society of Anesthesiologists (ASA) physical status classification of I to III prior to explantation of the infected prosthesis will be included in the study [13].

#### Exclusion criteria

Patients meeting any of the following criteria will be excluded from the study: Simultaneous participation in another interventional clinical trial involving drugs or medical devices will result in exclusion. Additionally, patients for whom the investigational implant components (femoral and/or acetabular) are deemed unsuitable due to anatomical or bone defect considerations, including cases requiring additional plate osteosynthesis, will not be eligible.

Patients with a previously implanted silver-coated device will also be excluded, as will those with immunodeficiency, such as individuals receiving immunosuppressive therapy or those with severe immunodeficiency requiring treatment. However, rheumatoid arthritis is explicitly not considered a reason for exclusion. Furthermore, patients undergoing active cancer treatment, including chemotherapy or radiation therapy, will not be included.

Severe soft tissue defects requiring local or free flap procedures, as well as periprosthetic joint infections with evidence of fungal infection, represent further exclusion criteria. Patients on indefinite antibiotic suppression therapy at the time of screening, defined as continuous administration of antibiotics with a non-curative intent, are not eligible. Similarly, individuals with a body mass index (BMI) greater than 40 kg/m^2^ will be excluded.

Based on the patient’s self-reported information and investigator assessment, women who are pregnant or breastfeeding, or those of childbearing potential not using adequate contraception, are ineligible for participation. Patients with known or self-reported hypersensitivity to silver or titanium will also be excluded.

Additional exclusions apply to patients held in custodial settings or correctional facilities and those in a dependent relationship with the sponsor, clinical site, or investigator. Contraindications to the investigational or comparator devices will also preclude participation. These include secondary diseases impacting the function of the joint implant, severe osteoporosis or osteomalacia, poor bone quality or osseous malformations that compromise the stability of joint replacement anchorage, non-regenerative bone conditions with insufficient proximal femoral support, and cases requiring prosthesis heads with neck length XXL.

### Who will take informed consent? {26a}

Informed consent will be obtained by a qualified investigator or by trained study personnel delegated by the principal investigator before any study-related procedures are performed. The process will involve a comprehensive explanation of the study aims, procedures, risks, benefits, and the participant’s rights, ensuring adequate time for questions and voluntary decision-making.

### Additional consent provisions for collection and use of participant data and biological specimens {26b}

Participants will provide consent for the collection, processing, and storage of personal and health data in compliance with GDPR and applicable data protection laws. Biological specimens collected during the study will only be used for the purposes defined in the protocol and will not be stored or analyzed beyond the scope of this trial.

## Interventions

### Explanation for the choice of comparators {6b}

The comparator devices selected for this study are non-IP-coated acetabular revision cups, acetabular augments, and revision hip stems, which represent the current standard of care for cementless revision hip arthroplasty and are CE-marked (Plasmafit^®^ Revision cup, Structan^®^ Augment, and Prevision^®^ Revision stem system, Aesculap, Tuttlingen, Germany). These implants are widely used in clinical practice and have established safety and performance profiles for hip arthroplasty revision.

Patients in the investigational group will receive IP-coated cementless acetabular cups, augments, and hip stems (Plasmafit^®^ Revision cup, Structan^®^ Augments, and Prevision^®^ Revision stem) during their revision hip arthroplasty procedure. Patients in the comparator group will receive non-IP-coated implants that are otherwise identical in design and mechanical properties to the investigational devices. All implants will be used in accordance with the manufacturer’s surgical manual and clinical guidelines. The surgical procedure will follow standard practices for revision hip arthroplasty, including preoperative planning, intraoperative implant positioning, and fixation. Patients can only be included if both the acetabular and femoral prostheses are exchanged, and the investigational devices are suitable for the revision procedure. Articulation options, including a modular dual mobility option, may be chosen according to patient-specific and surgical factors. The selection of implant sizes and components will be based on preoperative imaging and intraoperative assessment of patient anatomy and bone defects.

### Intervention description {11a}

The intervention is the implantation of a permanent implant. A revision will only be performed if necessary due to medical reasons. Both investigational and comparator devices will be implanted during a single surgical procedure performed as part of a one-stage or two-stage revision hip arthroplasty, depending on the clinical indication and surgeon’s preference. All patients will undergo the same preoperative preparation, intraoperative protocols, and postoperative follow-up procedures, ensuring consistency across the two groups. Follow-up visits will be conducted according to the study protocol, with data collected on infection rates, functional and radiological outcomes, pain levels, and safety parameters at predefined time points.

### Criteria for discontinuing or modifying allocated interventions {11b}

Discontinuation or modification of the assigned intervention will be considered in cases of serious adverse events, patient withdrawal of consent, or if continuing the assigned treatment is deemed medically inappropriate by the investigator. Any such decisions will be thoroughly documented, and alternative standard treatments will be provided as clinically indicated.

### Strategies to improve adherence to interventions {11c}

Adherence to the intervention protocol will be facilitated through comprehensive training of surgical and study staff, regular monitoring visits, and detailed documentation of all procedural steps in electronic case report forms (eCRFs). Any deviations from the protocol will be recorded and addressed promptly.

### Relevant concomitant care permitted or prohibited during the trial {11d}

Participants will receive concomitant care and medications based on clinical standards applicable to the treatment of PJI. No specific prohibitions on concurrent therapies unrelated to infection management exist.

Following completion of the trial, participants will be treated according to the standard of care practice of the treating surgeon.

### Provisions for posttrial care {30}

The sponsor will maintain an adequate insurance policy covering damages arising out of the clinical trial. This insurance covers the subjects with respect to the risks involved in this study according to the clinical investigational plan.

### Outcomes {12}

The primary endpoint is the infection-free survival rate, evaluated to demonstrate that revision hip implants with the antimicrobial silver coating significantly reduce the rate of periprosthetic reinfections within 12 months after hip revision arthroplasty. The primary variable is the occurrence of periprosthetic joint infection classified as “infection likely” or “infection confirmed” according to the European Bone and Joint Infection Society (EBJIS) criteria [11]. The time point for assessing this outcome is 12 months postoperatively, as the silver coating is designed to provide efficacy within this period. 

Secondary endpoints will be functional outcomes assessed using the Harris Hip Score (HHS) [14], focusing on pre- and postoperative scores to determine improvements in hip functionality, as well as quality of life evaluated through the EQ-5D-5L questionnaire [15]. Further, Kaplan-Meier implant survival will be determined for endpoints including septic revisions and all-cause revisions. Radiological outcome (hip stem migration, radiological signs of loosening, radiologic observations in the fixation area) will be evaluated using standardized X-rays. Safety outcomes including device failure, signs of systemic or local argyria, and (S)AEs and (S)ADEs will be documented. In addition, specific laboratory parameters related to liver (ALT, AST, GGT) and kidney (eGFR) function, as well as inflammatory markers (e.g., CRP, leukocytes), silver ion in peripheral blood and drainage liquid, and surgery-related data, including bone defect classification, length of stay, and antibiotic therapy details will be evaluated.

### Participant timeline {13}

The clinical investigation covers eight study-related visits (Fig. 1): one preoperative visit, the surgery itself (implantation of the investigational or comparator device), and six postoperative (p.o.) visits. All visits are within the frame of clinical standard visits. An overview of the schedule of enrollment, interventions, and assessments is shown in Table 1.

**Fig. 1 Fig1:**
[figure not shown]
Planned study visits

**Table 1 Tab1:** Participant timeline: schedule of enrollment, interventions, and assessments

		Post-randomization			Follow-Up			
Timepoint	*−**7 to **−**2*	0	*1 to 3 days*	*2 weeks*	*6 weeks*	*6 months*	*12** months*	*24** months*
Enrollment								
Eligibility screen	X							
Informed consent	X							
Randomization	X							
Intervention/comparator								
*IP-coated device*		X						
*Non-IP-coated device*		X						
Assessments								
*Infection-free implant survival rate (signs of required revision)*			X	X	X	X	X	X
*Harris-Hip-Score, Eq-5D-5L*	X		X	X	X	X	X	X
*Radiological outcome (hip stem migration, signs of loosening, fixation) *via* X-rays*		X		X			X	X
*Safety (laboratory blood parameter, signs of systemic or local argyria, (S)AEs/(S)ADE, device failure)*			X	X	X	X	X	X

### Sample size {14}

The sample size calculation for this study is based on the 1-year event rate of PJI in the comparator group, assumed to be 21.5%. This assumption is derived from a custom analysis of the EPRD (German Arthroplasty Registry) data [1], which documents revision procedures where implant components are exchanged, including Kaplan–Meier estimates for re-revision rates (total, infection related, and non-infection related) at 6, 12, and 24 months. Specifically, the re-revision rate due to periprosthetic infection within 12 months, for procedures involving combined exchange of stem and cup, was reported as 16.4%. However, this figure only accounts for cases where reinfections resulted in implant exchange and does not fully capture all events classified under the EBJIS criteria (“infection likely” or “infection confirmed”). To address this, a correction factor of 1.33 was applied to account for cases of reinfection treated with alternative approaches, such as antibiotic suppression therapy, implant retention surgery (DAIR), amputation, or where infection was not documented at the time of registry entry. After this adjustment, the estimated event rate in the comparator group increased to 21.5%.

In the intervention group, the event rate is assumed to be 8.6%, reflecting an anticipated 60% reduction in the rate of periprosthetic reinfections. The effect size estimation is based on the estimated reduction of periprosthetic infections in humans by 90% (unpublished case series), a reduction of periprosthetic infections in a rabbit model by 65% [16], and a reduction of infections in canine osteosynthesis implants by 73% (unpublished manufacturer data) or by 39% in the same canine implant type based on a different study [17].

Using a one-sided chi-square test for independent two-sample proportions with a significance level of *α* = 0.025 and a power of 80%, the study requires 240 participants (120 per group) to meet the primary endpoint. To account for a 10% drop-out rate, a total of 268 patients will be enrolled, with 20 patients allocated to part A and 248 patients to part B. Sample size was calculated using SAS (SAS VIYA software version V.04.00, SAS Institute Inc., Cary, NC, USA).

The above chi-squared based sample size calculation was used, although log-rank tests are used for primary hypothesis tests. A comprehensive simulation-based sample size calculation using the log-rank statistics under variation of the underlying hazard function found a small to marginal increase in power compared to the chi-squared statistic.

As predefined in the protocol, an extension of the total sample size of up to 50% is allowed, which results in a maximum of 400 patients (360 patients + 10% dropout). The 50% limit was determined based on practical considerations. This results in 20 patients scheduled for the safety phase (part A) and up to 380 patients scheduled for the main phase (part B).

The sample size re-estimation will be based on all available data of the first 134 treated patients, limited to their 12 months follow-up visit (“right truncated”). By estimating the per-group hazard, based on the corresponding survival data, the conditional power for detecting the difference in primary outcome between the two groups in the final analysis will be re-estimated. Details can be found in Wassmer and Brannath [18]. In case the intended number of 268 study subjects yields a conditional power smaller than 80% for the log-rank test in the final primary analysis, the number of subjects to be included in the study is increased up to the prespecified limit of 400 patients. When the conditional power based on the initially planned 268 patients is 80% or above, the clinical investigation will continue using the planned sample size. If the conditional power is very small (e.g. < 10%), the study will be completed with the originally estimated sample size.

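### The control event rate does not follow from its stated inputs: 16.4% × 1.33 = 21.8%, not 21.5%; the three figures must be reconciled, with no change to enrolment

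*Protocol article*

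**What the plan says.** All the figures are in the Sample size {14} section of the protocol article.

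- **Starting rate.** A custom analysis of the German Arthroplasty Registry supplies the 12-month re-revision rate for periprosthetic infection, which "for procedures involving combined exchange of stem and cup, was reported as 16.4" per cent.
- **Adjustment.** The registry counts only reinfections that led to implant exchange, so "a correction factor of 1.33 was applied to account for cases of reinfection treated with alternative approaches" (suppression therapy, implant retention, amputation, or infection not documented at registry entry).
- **Result.** "After this adjustment, the estimated event rate in the comparator group increased to 21.5" per cent. The section also opens with this figure: the calculation is "based on the 1-year event rate of PJI in the comparator group, assumed to be 21.5" per cent.
- **Treatment arm.** There "the event rate is assumed to be 8.6%, reflecting an anticipated 60% reduction in the rate of periprosthetic reinfections".
- **Sample size.** "Using a one-sided chi-square test for independent two-sample proportions", "with a significance level of *α* = 0.025 and a power of 80" per cent, "the study requires 240 participants (120 per group) to meet the primary endpoint". Allowing 10% drop-out, 268 are enrolled.

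No step other than the factor of 1.33 is described between 16.4% and 21.5%, and no unrounded input is given.

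**The concern.** The text gives a complete two-factor derivation, and the product of the two factors is not the printed result. The treatment-arm rate is 0.4 times the control rate, and the number per arm is computed from the pair, so the control rate feeds everything that follows.

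The adjustment also matters to the design. Had the unadjusted 16.4% been used with the same 60% reduction (16.4% against 6.56%), the formula used below would ask for 164 per arm, and 120 per arm would have about 67% power. A reader should therefore be able to follow how 16.4% became the planning rate, and as printed cannot. The Discussion presents the registry basis of the sample size as a strength of the study, which is a further reason for the line to reproduce.

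**Working it through.** **1. Reproduce the plan's sample size from its own rates.** Inputs from Sample size {14}: p_C = 0.215, p_T = 0.086, one-sided α = 0.025, power 80%. Allocation is 1:1 (Trial design {8}). Formula: two-proportion test with pooled variance under the null and no continuity correction,

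n per arm = [1.960·√(2p̄(1−p̄)) + 0.842·√(p_C(1−p_C) + p_T(1−p_T))]² / (p_C − p_T)², with p̄ = (p_C + p_T)/2.

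- p̄ = 0.1505; √(2p̄(1−p̄)) = 0.5057; second root = 0.4974; difference = 0.129.
- n = (1.4097 / 0.129)² = 119.4, so 120 per arm and 240 in total. This agrees with the plan.
- Power at 120 per arm = Φ[(0.129·√120 − 1.960·0.5057) / 0.4974] = Φ(0.849) = 80.2%.
- Drop-out: 120 / 0.9 = 133.3, so 134 per arm and 268 in total. This agrees with the plan.
- Treatment-arm rate: 0.4 × 21.5% = 8.6%. This agrees with the plan.

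Everything from 21.5% onward is sound.

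**2. Recompute the control rate.** 16.4% × 1.33 = 21.81%. The plan states 21.5%.

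**3. Test whether rounding explains the gap.**

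- Lowest product of values that print as 16.4% and 1.33: 16.35% × 1.325 = 21.66%.
- Highest: 16.45% × 1.335 = 21.96%.
- Working back, a result that rounds to 21.5% (21.45% to 21.55%) needs a factor between 21.45/16.45 = 1.304 and 21.55/16.35 = 1.318, or a starting rate between 21.45/1.335 = 16.07% and 21.55/1.325 = 16.26%. No value in either range rounds to the printed input.

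**4. Test other ways the factor might have been applied.**

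| Reading | Control rate |
|---|---|
| Factor 4/3, or division by 0.75 | 21.87% |
| Factor on the cumulative hazard: 1 − (1 − 0.164)^1.33 | 21.20% |
| Factor on the odds | 20.69% |

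None gives 21.5%.

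**5. Size of the effect if 16.4% and 1.33 are right.** Keep the 60% reduction: 21.81% against 0.4 × 21.81% = 8.72%.

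| Control / treatment rate | n per arm | Total | Power at 120 per arm |
|---|---|---|---|
| 21.5% / 8.6% (as stated) | 119.4 → 120 | 240 | 80.2% |
| 21.81% / 8.72% (product of stated inputs) | 117.4 → 118 | 236 | 80.9% |

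The difference is 4 patients in 240 and 0.7 percentage points of power.

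**The case against.** The best case on the other side is that this is an editorial slip with no consequence. Much of that stands. The gap is 0.3 percentage points, small beside the published reinfection rates of 3.7% to 23.3% listed in the Background and beside the element of judgement in any such correction factor. If the slip is in the factor or the registry rate as printed, then 21.5% was the intended planning rate, and 8.6%, 240 and 268 are all correct. What does not stand is leaving the line as it is, because the three figures in one paragraph cannot all be right without a further step.

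A reader might infer more than the documents support, in four ways.

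- **That the sample size is wrong or the trial underpowered.** It is not. The size reproduces from 21.5% and 8.6%, and if the product is used instead, the size is slightly generous.
- **That interim analysis II measures observed hazards against 21.5%.** The Sample size section says that conditional power is calculated from per-group hazards estimated from the trial's own data and compared with 80% and with a very low value such as 10%. The planning rate enters only indirectly, because it produced the 268 at which conditional power is evaluated.
- **That the control rate is the only empirical input.** The 60% reduction is also an input, and the section rests it on a human case series, a rabbit model and two canine sources.
- **That the factor should read 1.31 or the registry rate 16.2%.** These are back-solved from 21.5% (21.5/16.4 and 21.5/1.33). The registry analysis is not shown, so neither can be prescribed.

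**Conclusion.** The inconsistency is certain as printed. The stated inputs give 21.8%, input rounding cannot bring that to 21.5%, and so at least one of the registry rate, the factor and the control rate is wrong, or a step has been left out. The documents do not show which.

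Its consequence is small and conservative: between none (if 21.5% is right) and 0.7 points of extra power at the planned size (if 16.4% and 1.33 are right). This rests on the chi-square formula without continuity correction, which reproduces the plan's 120 per arm, and on keeping the 60% relative reduction. It is a documentation error worth correcting because the planning rate cannot be traced, and not a reason to change the design.

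**What to change.** Check the registry rate, the correction factor and the control rate against the source analysis, then correct the wrong figure or state the missing step.

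- **If 16.4% and 1.33 are right:** state the control rate as 21.8% and the treatment-arm rate as 8.7% (same 60% reduction), and give the power at 120 per arm as about 80.9%, noting that 118 per arm would suffice.
- **If 21.5% is right:** correct the factor or the registry rate to the value in the source. The 8.6%, 240, 268 and 80.2% power then stand.

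The cost is one look-up and a corrected sentence. Enrolment, the ceiling of 400 and the interim II rule need no change on this account.
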